## Background

Total hip replacement (THR) is the preferred method for the active and lucid elderly patient with a displaced femoral neck fracture (FNF) [1, 2]. Comparisons between cemented and uncemented stems in hip arthroplasty for patients with a FNF have almost consistently favoured cemented fixation, mainly because of greater deterioration in pain, walking ability, use of walking aids and activity of daily living [3] and because of a higher incidence of hip related complication such as periprosthetic fracture [4] for uncemented implants. Despite this, recent reports on modern, hydroxyapatite-coated femoral stems used for this patient-group have shown promising early results [5-7]. In addition, bone cement implantation syndrome (BCIS), is more prevalent in cemented than in uncemented stems [8]. It is also a commonly occurring phenomenon in patients treated for FNF with cemented arthroplasty and severe BCIS has a significant impact on early and late mortality [9]. Thus, the use of uncemented stems for this patient group may still be justified.

We hypothesized that an uncemented, proximally porous and hydroxyapatite coated femoral stem used in THR for a displaced FNF would not be associated with more adverse peri- and postoperative hip-related complications compared with a THR using cemented stem, and that the health-related quality of life for the patients would be equivalent at 2 years.

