### Sample size and power analysis

Prior to the study start, a sample size calculation was done. To show non-inferiority with 80 % power of the primary endpoint all hip-related complications between the two groups, assuming a total complication rate of 20 %, and with a non-inferiority limit of 15 % requires 60 patients in each group. The assumed 20 % complication rate includes also minor hip-related complications as per previously published papers ranging between 10 and 20 % [1, 2, 6]. To show non-inferiority with 80 % power of the primary variable health related quality of life – HRQoL, as measured with EQ-5D requires 40 patients in each group, and with a non-inferiority limit of 0.1, assuming a value of 0.73 (SD 0.18) 1 year after the surgery [5]. The alpha (2-tailed) is set at 0.025 since we have two endpoints for the power calculation. Since this patient group has a 1-year mortality of 10 %, 70 patients in each group should be sufficient for the study.

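### The hypothesis joins complications and EQ-5D, the alpha split treats them as separate claims, and the stated inputs give about 36–45% power for both, not 80%

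*Protocol article*

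**What the plan says.** In the Protocol article, Background, the hypothesis has two parts joined in one sentence. The first concerns complications: the uncemented stem "would not be associated with more adverse peri- and postoperative hip-related complications compared with a THR using cemented stem". The second part, on patient-reported health, is attached to it without a break: "and that the health-related quality of life for the patients would be equivalent at 2 years". Both outcomes are listed as primary endpoints under Outcome measurements.

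The section Sample size and power analysis treats them one at a time:

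- Complications: "To show non-inferiority with 80 % power of the primary endpoint all hip-related complications between the two groups", with an assumed total rate of 20%, and "with a non-inferiority limit of 15 % requires 60 patients in each group".
- Quality of life: "To show non-inferiority with 80 % power of the primary variable health related quality of life", with a limit of 0.1, an assumed mean of 0.73 and SD of 0.18, giving 40 per group.
- Type I error: "The alpha (2-tailed) is set at 0.025 since we have two endpoints for the power calculation".
- Conclusion: after an allowance for 10% one-year mortality, "70 patients in each group should be sufficient for the study".

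The article does not say whether the trial succeeds on one endpoint or only on both, and it gives no joint power.

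**The concern.** Dividing alpha between two endpoints protects against a false positive when either endpoint alone can support a claim. If both endpoints must succeed, each can be tested at the full level without inflating the overall error, and the division only lowers power. The Background wording points to the second rule and the alpha to the first. Until they are reconciled, it is unclear what the planned 70 per group is meant to be enough for.

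The size of the problem depends on what power 70 per group really gives. If it is well below 80%, an uncemented stem that truly meets both criteria would often fail to be shown to do so. That failure could be misread as evidence against the stem.

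**Working it through.** **Inputs, all from Sample size and power analysis.** Complications: 20% in both arms, margin 0.15. EQ-5D: SD 0.18, margin 0.1. Alpha two-tailed 0.025, that is 0.0125 in the non-inferiority direction (z = 2.241). Power 80% (z = 0.842). Planned 70 per group; 70 × 0.9 = 63 after the stated mortality.

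**Assumptions.** No true difference between arms. Complications are evaluable in 63 to 70 per group, since a complication may be counted before a death; EQ-5D in 63. The protocol gives no correlation between the endpoints, so 0 to 0.5 is shown. EQ-5D is treated as non-inferiority, as in the sample size section.

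**Step 1: the plan's own sizes.**

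- Complications: n = 2 × 0.2 × 0.8 × (2.241 + 0.842)² / 0.15² = 0.32 × 9.505 / 0.0225 = 135.2, so 136 per group. Printed: 60.
- EQ-5D: n = 2 × 0.18² × 9.505 / 0.1² = 61.6, so 62 per group. Printed: 40.

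At one-sided 0.025 the sizes are 112 and 51; at one-sided 0.05, 88 and 41. So the EQ-5D figure is approached only at a looser alpha than stated, and the complications figure at none of these. The mortality allowance is sound: 60 / 0.9 = 67, below 70.

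**Step 2: power for each endpoint.** Power = Φ(margin / SE − z).

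- Complications, n = 63: SE = √(0.32 / 63) = 0.0713; 0.15 / 0.0713 = 2.105; Φ(2.105 − 2.241) = 44.6%.
- Complications, n = 70: SE = 0.0676; Φ(2.219 − 2.241) = 49.1%.
- EQ-5D, n = 63: SE = 0.18 × √(2 / 63) = 0.0321; Φ(3.118 − 2.241) = 81.0%.

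**Step 3: power for both.** With independence this is the product; otherwise it comes from a bivariate normal distribution. The two-tailed 0.05 rows use z = 1.960.

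| Evaluable per group (complications / EQ-5D) | Two-tailed alpha | Complications | EQ-5D | Both, r = 0 | Both, r = 0.5 |
|---|---|---|---|---|---|
| 63 / 63 | 0.025 | 44.6% | 81.0% | 36.1% | 41.3% |
| 70 / 63 | 0.025 | 49.1% | 81.0% | 39.7% | 45.2% |
| 63 / 63 | 0.05 | 55.8% | 87.7% | 48.9% | 53.0% |
| 70 / 63 | 0.05 | 60.2% | 87.7% | 52.8% | 57.0% |

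**Step 4: how much is due to requiring both.** At two-tailed 0.025, complications alone falls 31 to 35 points short of 80% (80 − 49.1 and 80 − 44.6). Requiring EQ-5D as well takes off a further 3 to 9 points (44.6 − 41.3 up to 49.1 − 39.7).

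**Step 5: if both printed sizes were right.** Give each endpoint 80% power at its own printed size and scale its signal by √(n / 60) or √(n / 40). At one-sided 0.0125:

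| Evaluable per group | Complications | EQ-5D | Both, r = 0 to 0.5 |
|---|---|---|---|
| 60 / 60 | 80.0% | 93.8% | 75.0–77.3% |
| 63 / 63 | 82.1% | 94.8% | 77.8–79.7% |
| 70 / 63 | 86.2% | 94.8% | 81.7–83.4% |

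At one-sided 0.025 the first row becomes 74.4–76.8%, so the overall range is about 74–83%.

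**The case against.** The strongest reply is that a both-must-succeed rule is inferred. The Background sentence states expectations and sets no decision rule. The endpoints are numbered separately, and splitting alpha is the usual design for separate claims, for which marginal power is the right figure to report. The success rule may also be set out in a fuller document that is not shown. This stands to the extent that the article cannot be said to require both endpoints. It does not remove the inconsistency: the article itself fixes alpha under one rule and words its hypothesis under the other.

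A second reply is that the low joint power comes mainly from a different error, the complications sample size. That is correct, and Step 4 shows it. Even so, the 80% stated for complications is not delivered under either rule.

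A reader might also multiply the two printed 80% figures and conclude that joint power is at most 64%, or about 69% with correlation 0.5, even if the printed sizes were right. The document does not support this. The 80% for EQ-5D belongs to 40 per group, and the trial plans 70. Step 5 shows that, with both printed sizes taken as correct, the joint requirement would cost little or nothing. Nor would 64–69% be a ceiling: two tests with 80% power each have a joint power of up to 80%, depending on their correlation.

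**Conclusion.** The point holds as an unreconciled success rule together with an overstated power. The hypothesis is worded as a conjunction, alpha is split as for an either-endpoint claim, and no power is stated for the hypothesis as worded. On the stated inputs at two-tailed 0.025, power is about 45–49% for complications, 81% for EQ-5D and 36–45% for both. EQ-5D alone is therefore adequately powered at 70 per group; complications is not, and it dominates the joint result.

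The figures rest on no true difference between arms, normal-approximation non-inferiority tests, 63–70 evaluable per group for complications and 63 for EQ-5D, and a correlation of 0 to 0.5. At the stated alpha, even perfect correlation could not lift joint power above the 45–49% for complications alone.

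**What to change.** State the success rule in Sample size and power analysis, and make the Background hypothesis match it.

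- **If both endpoints must succeed:** say so, drop the alpha split, test each endpoint at two-tailed 0.05, and replace the statement that 70 per group is enough with the joint power of about 49–57%, giving the assumed correlation.
- **If either endpoint may carry a claim:** keep two-tailed 0.025 for each, reword the Background as two separate hypotheses, and restate the marginal powers as about 45–49% for complications and 81% for EQ-5D.

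Either way, the cost is some wording, one short calculation and a less favourable stated power. No extra patients are needed for this change. Restoring 80% power for complications is a separate decision and would need a larger trial: 136 evaluable per group at the stated alpha, or 112 at two-tailed 0.05, for that endpoint alone.

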### Analysis

Analyses of outcome are based on the intention-to-treat principle and all patients remain in their randomized group regardless of any further surgical intervention. Patients with missing data (i.e. EQ-5D, HHS VAS etc.) at any of the follow-ups are analysed with the last observation carried forward (imputed). Descriptive statistics (means and standard deviations) will be used to describe the patient characteristics and outcome variables at the measurement points. Fisher’s exact test will be used to test the primary endpoint. We will use the Student’s *t*-test and Levene’s test for comparison of the functional outcomes with 95 % CI presented. We will use Kaplan-Meier survival curves with log-rank test for patient and hip re-operation survival analysis. The analyses will be performed with SPSS 22.0 for Mac (SPSS, Chicago, Illinois) statistical software.

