### Study subjects and eligibility criteria

All patients with a displaced FNF who are admitted to Danderyd Hospital will be screened for participation in the study. Research nurses who identify eligible patients before surgery screen all patients at arrival to the hospital. The first author ([name]) or one of the other co-authors will include patients and acquire informed consent. All who agree to participate and give their oral and written informed consent will be included if they fulfil the inclusion criteria. The inclusion criteria are an acute (within 48 h) displaced FNF (Garden III to IV) [13] after a low-energy trauma (i.e. fall), an age 65–79 years, no concurrent joint disease or previous fracture in the lower extremities, an intact cognitive function (no diagnosis of dementia and at least seven correct answers on a ten-item Short Portable Mental Status Questionnaire [14], ability to ambulate independently with or without the help of walking aids. The age limits for THR (65–79 years) are standard in our hospital and in most Swedish hospitals. We will exclude patients with pathological fractures, and those with rheumatoid arthritis or symptomatic osteoarthritis of the hip. We will also exclude those who, because of severe co-morbidities, are deemed not suitable for a THR by the anaesthesiologist, and those who are unsuitable to participate in the study for any other reason (substance abuse, alcoholism). Based on our previous experience in randomized clinical trials in this population, [1, 5] we expect to include and receive informed consent from approximately half of the target population (i.e. 65–79 years and fulfilling other inclusion criteria).

The baseline data of the patients’ health-related quality of life and hip function will be obtained retrospectively for the last week.

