### Outcome measurements

#### Primary endpoints

The primary endpoints will be 1) the incidence of all hip-related complications up to 2 years after surgery and 2) change in health-related quality of life assessed with EQ-5D index (EuroQol) [16] up to 2 years. Hip-related complications are defined as intra- and postoperative periprosthetic fractures, dislocation, wound infection both superficial and deep, loosening both early and late and revision of any prosthetic implant for any reason.

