### Data collection and follow-ups

The primary assessment will establish that the patient fulfils all inclusion/exclusion criteria and identify any comorbidity. The patients will then be interviewed by a research nurse regarding living conditions, mobility, activities of daily living (ADL) [22], status and health-related quality of life according to the EQ-5D during the last week before the fracture as a baseline. For all primary and secondary endpoints including ADL the patients themselves will be providing data during the study period. It is obvious that the patients’ ability to record this correctly while awaiting urgent surgery may be questioned. It is, however, impossible to collect these data in a prospective manner and the method is regularly used in patients with a fracture of the hip [1, 2, 19]. Patients who are unable or unwilling to attend follow-ups will be interviewed by telephone or they will send their answers by mail. We will use the unique Swedish personal id-number and collect data prospectively throughout the study period through a combination of a search of our databases, follow-ups and the Swedish Hip Arthroplasty Register. Non hip-related adverse events (AEs) and serious adverse events (SAEs) will be collected throughout the study period (2 years). Although the primary endpoints will be evaluated at 2 years, the study will also include a 4 and 10-year follow-up. The study visits are presented in Table 1.

**Table 1 Tab1:** All visits in the study

	d 0	d 0	0	+1 d	+4 d	5d	3 m.	1 y	2 y	4 y	10 y
	Screening	Inclusion	Randomization and surgery	POD1	POD4	End of In-pt stay	Follow-up	Follow-up	Follow-up	Follow-up	Follow-up
Screening for eligibility	x										
Informed consent		x									
Baseline data		x									
Randomization			x								
X-ray	x			x				x	x	x	x
HHS		x						x	x	x	x
VAS		x						x	x	x	x
EQ-5D		x						x	x	x	x
Adverse events			x	x		x	x	x	x	x	x
Intraoperative			x								
Blood test		x		x	x		x				

X-ray = anterioposterior and lateral radiographs, HHS = Harris hip score, EQ-5D = Quality of life score, Intraoperative = Intraoperative measurements including blood pressure, puls rate, pulse oxyometry before, during and after femoral stem insertion, VAS = Visual Analogue Scale for hip pain, Bloodtest = C-reactive protein (CRP), IL-6, Hb, D-dimer

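### Last observation carried forward scores a patient lost before 1 year as having no loss of quality of life, because the only earlier EQ-5D is the recalled pre-fracture value

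*Protocol article*

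**What the plan says.** All references are to the protocol article.

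- **Analysis** fixes the missing-data rule: "Patients with missing data (i.e. EQ-5D, HHS VAS etc.) at any of the follow-ups are analysed with the last observation carried forward (imputed". The same section sets the analysis population: "Analyses of outcome are based on the intention-to-treat principle and all patients remain in their randomized group". It makes no exception for deaths and does not bar carrying a baseline value forward.
- **Primary endpoints** names as the second primary endpoint "change in health-related quality of life assessed with EQ-5D index (EuroQol", followed to 2 years.
- **Data collection and follow-ups** defines the baseline as "health-related quality of life according to the EQ-5D during the last week before the fracture as a baseline". **Study subjects and eligibility criteria** confirms that these data "will be obtained retrospectively for the last week".
- **Table 1** marks EQ-5D at inclusion, 1, 2, 4 and 10 years. The columns for the in-hospital days, end of stay and 3 months have no EQ-5D.
- **Sample size and power analysis** sets a non-inferiority limit of 0.1 for EQ-5D with SD 0.18. It justifies 70 per group with the words "Since this patient group has a 1-year mortality of 10" per cent.

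**The concern.** Carrying a value forward is only as sensible as the value carried. Here, anyone without a 1-year assessment has a single EQ-5D on file, and it describes health before the injury. Carried forward, it makes the change exactly zero, as if the patient had recovered completely.

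The trial aims to show that the uncemented stem is not worse. Pre-fracture scores carry no treatment effect, because randomization makes them equal in expectation between arms. If similar shares of both arms receive them, any true deficit shrinks, and in a non-inferiority comparison that makes a wrong positive conclusion easier to reach.

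The sections also fit together poorly. The sample size is enlarged because early deaths are expected to supply no data, while the analysis rule, read literally, returns those patients to the data set with a favourable score.

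**Working it through.** **Inputs from the document.** 70 per arm; margin 0.1; SD 0.18; cemented mean 0.73 at 1 year; alpha 0.025 two-tailed, so 0.0125 in the non-inferiority tail (z = 2.2414); 80% power; 10% mortality at 1 year, or 0.10 × 70 = 7 patients per arm.

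**Assumptions not in the document.** For the unequal-attrition cases and the simulation only: mean pre-fracture EQ-5D B between 0.80 and 0.90, SD 0.18, correlation 0.5 with follow-up.

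**The plan's own figure.** n per arm = 2 × (z for alpha + 0.8416)² × 0.18² / 0.1². This gives 62 at one-sided 0.0125, 51 at 0.025 and 41 at 0.05. The stated 40 is approached only at one-sided 0.05. That is a separate matter, but it is why results are shown below at two levels.

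**Equal attrition.** Let a share m of each arm carry baseline forward, and let the true deficit equal the margin.

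- Expected difference = 0.10 × (1 − m), on level or change scores.
- SE = 0.18 × √(2/70) = 0.0304.
- False non-inferiority rate = Φ(−z + 0.10 × m / SE).
- At m = 10%: Φ(−2.2414 + 0.010/0.0304) = Φ(−1.913) = 2.8%.

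| m in each arm | Expected difference | Rate at one-sided 0.0125 | Rate at one-sided 0.025 |
|---|---|---|---|
| 0% | 0.100 | 1.25% | 2.5% |
| 5% | 0.095 | 1.9% | 3.6% |
| 10% | 0.090 | 2.8% | 5.1% |
| 15% | 0.085 | 4.0% | 7.1% |
| 20% | 0.080 | 5.7% | 9.6% |

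Only the 10% row corresponds to a figure in the document. Simulation (20,000 trials per scenario, pooled t interval) gives 2.5% to 2.9% for that row, on level and change scores alike.

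**Unequal attrition.** With shares mU (uncemented) and mC (cemented), and true means 0.63 and 0.73:

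- Bias in the difference = mU × (B − 0.63) − mC × (B − 0.73). A positive value favours the uncemented stem.
- 15% uncemented, 5% cemented: at B = 0.80 the bias is 0.0255 − 0.0035 = +0.022, and at B = 0.90 it is 0.0405 − 0.0085 = +0.032. The simulated false non-inferiority rate is 6% to 11%.
- 5% uncemented, 15% cemented: at B = 0.80 the bias is 0.0085 − 0.0105 = −0.002, and at B = 0.90 it is 0.0135 − 0.0255 = −0.012. The simulated rate is 0.4% to 1.0%, below nominal.
- The sign changes when mC/mU exceeds (B − 0.63)/(B − 0.73), which is 2.4, 1.8 and 1.6 for B = 0.80, 0.85 and 0.90.

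**Without carrying baseline forward.** With 10% missing at random, 63 per arm are observed. The expected difference is −0.100 and the simulated rate is 1.2% to 1.3%, the nominal level. Power at no true difference = Φ(0.1/(0.18 × √(2/63)) − 2.2414) = Φ(0.877) = 81%.

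**The case against.** **Deaths are not named.** The rule speaks of missing data at follow-ups, and the sample-size section treats deaths as lost. The two agree if the rule covers only missed assessments and the dead are left out. How deaths enter a quality-of-life analysis is often settled in the analysis plan, which is not shown. This stands as a limit on the claim: a reader might infer that the protocol definitely scores the dead as recovered, but it only fails to exclude that. It does not rescue the rule for survivors with no 1-year value, for whom the text and Table 1 leave no other reading.

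**The size leans on that reading.** The only documented 10% is mortality. If deaths are excluded, early dropout remains. The document gives no rate for it, and telephone and mail follow-up will keep it down. This also stands. Compounding two years of mortality to 1 − 0.9² = 19% would be wrong here, since a patient who dies in year 2 after a 1-year assessment carries the 1-year value.

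**The direction is not fixed.** A reader might infer that the rule always helps the uncemented stem, and that deaths from bone cement implantation syndrome, raised in the Background, make this worse. The reverse is true: extra deaths in the cemented reference arm would earn that arm favourable scores and, if the excess is large enough, bias against non-inferiority.

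**The remedy has limits.** A model with baseline as covariate gains nothing from patients without a post-operative EQ-5D. Scoring death as 0 also gives both arms a common value. At 10% deaths the difference is again 0.090, and with SE = √((0.0771 + 0.0649)/70) = 0.0450 the rate is about 2.2%. So dilution is not peculiar to carrying forward. What is peculiar to it is crediting death or early loss as no loss at all.

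**The test is not spelled out.** The t-test is assigned to functional outcomes, and the Abstract mentions a regression model. The point does not depend on which test is used for EQ-5D.

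**Conclusion.** The point holds in a bounded form. The stated rule combined with the stated schedule gives a wrong value to every patient without a 1-year EQ-5D and affects a co-primary endpoint.

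With similar attrition, it moves the result towards non-inferiority. The false non-inferiority rate roughly doubles, from 1.25% to about 2.8%, if 10% of each arm carry baseline forward. That figure assumes 70 per arm, SD 0.18, a true deficit exactly at the 0.1 margin, and that year-1 deaths fall under the rule. If they do not, the inflation is smaller, by an amount the document does not allow one to state.

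The documents do not support a claim of bias in one direction whatever the attrition. With pre-fracture EQ-5D assumed at 0.80 to 0.90, cemented attrition above about 1.6 to 2.4 times the uncemented rate would reverse it. A bias whose sign depends on which arm loses more patients is still a reason to drop the rule.

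**What to change.** 1. In Analysis, remove last observation carried forward for the primary EQ-5D comparison and state that the pre-fracture value is never used as an outcome.
2. Analyse the observed 1- and 2-year EQ-5D with a likelihood-based repeated-measures model, with baseline EQ-5D and sex (the stratification factor) as covariates.
3. Reconcile Sample size and power analysis with Analysis by stating that values after death are not imputed by carrying forward.
4. Add one sensitivity analysis with EQ-5D set to 0 after death, so that unequal mortality no longer earns credit for the arm with more deaths.

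The cost is analysis wording and one extra model run. Patients with no post-operative EQ-5D will not contribute to the main model, but the power shown above does not depend on them. Collecting EQ-5D at the existing 3-month visit would be a useful extra, not a substitute: it cannot help patients who die before that visit or who have already passed it.

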**Methods/design:**

In a single-centre, single-blinded, randomized controlled trial, we will include 140 patients aged 65-79 years with an acute displaced FNF and randomize them in a 1:1 ratio to a cemented tapered or a uncemented tapered hydroxyapatite - coated femoral stem. A cemented cup will be used in both groups. The patients will be blinded for allocation. The primary endpoints will be the incidence of all hip-related complications and health-related quality of life evaluated with EuroQol-5D (EQ-5D) index up to 2 years after surgery. Secondary outcomes will be overall mortality, general medical complications and hip function. The follow-up will be at 3 months, 1 and 2 years. Further follow-ups after end of study will be at 4 and 10 years. Results will be analysed using 95 % CI’s for the effect size. A regression model will also be used to adjust for stratification factor.

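### Hip-related complications are framed and sized for non-inferiority with a 15% limit, but the only test named for them in the Analysis section, Fisher's exact test, does not use that limit

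*Protocol article*

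**What the plan says.** **Hypothesis (Background).** The uncemented stem "would not be associated with more adverse peri- and postoperative hip-related complications compared with a THR using cemented stem". This is a one-directional, not-worse-than claim.

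**Sample size and power analysis.** The stated aim is "To show non-inferiority with 80 % power of the primary endpoint all hip-related complications between the two groups", "assuming a total complication rate of 20" per cent and "with a non-inferiority limit of 15 % requires 60 patients in each group". On the error rate: "The alpha (2-tailed) is set at 0.025 since we have two endpoints for the power calculation". The total is then raised to 70 per group for mortality.

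**Analysis.** Fisher's "exact test will be used to test the primary endpoint". The section gives no limit, no one-sided test and no rule comparing a confidence bound with 15%. Its 95% interval belongs to the sentence on functional outcomes.

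**Abstract, Methods/design.** Results are to be analysed with 95% confidence intervals for the effect size, and "A regression model will also be used to adjust for stratification factor". Neither statement refers to the limit. The 15% figure appears only in the sample size section.

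**The concern.** The trial is designed around one hypothesis and the named test addresses another. Fisher's test, as ordinarily used, has equal rates as its null hypothesis. A non-significant result does not exclude an excess of 15 points with the uncemented stem. A significant result does not by itself show that the excess reaches 15 points. The p value therefore cannot settle the question the trial was sized for, in either direction.

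The risk lies on the unsafe side. In a trial of this size a non-significant Fisher result is likely even when the uncemented stem is worse by the full limit, and such a result is easily reported as support for the hypothesis. With no stated rule linking an interval to the limit, the rule could also be chosen after the data are seen.

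**Working it through.** **Inputs from the article.** Complication rate 20%; limit 15%; 80% power; two-tailed alpha 0.025; 60 per group, raised to 70; 1:1 allocation.

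**Assumptions.** The 20% is the cemented rate, and also the uncemented rate where the arms are taken as equal. The limit is in absolute percentage points. All 70 patients per group are evaluable.

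**1. The plan's own figure.** For a true difference of zero, n per group = (z₁₋ₐ + z₀.₈₀)² × 2p(1−p) / limit², where a is the one-sided level. Two-tailed 0.025 corresponds to one-sided 0.0125:

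(2.241 + 0.842)² × 2 × 0.20 × 0.80 / 0.15² = 9.505 × 0.32 / 0.0225 ≈ 135.2, so 136 per group.

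One-sided 0.025 gives 112, 0.05 gives 88 and 0.10 gives 65. The stated 60 is not reproduced. That is a separate matter and bears on this point only through the cost of the fix.

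**2. What Fisher's test does at the limit.** Let the true rates be 35% (uncemented) and 20% (cemented), an excess of exactly 15 points, so a conclusion of non-inferiority would be wrong. All pairs of binomial counts with 70 per group were enumerated. For the interval rule, non-inferiority is declared when the Newcombe upper limit is below 15 points.

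| Level | Fisher non-significant | Newcombe rule declares non-inferiority |
|---|---|---|
| 0.025 (97.5% interval) | 67.1% | 1.4% |
| 0.05 (95% interval) | 56.1% | 2.7% |

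With 60 evaluable per group the Fisher column becomes 72.9% and 62.5%. The Newcombe column is unchanged to this precision.

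**3. An example.** Take 20/70 against 12/70.
- Difference: 0.2857 − 0.1714 = 0.1143, or 11.4 points.
- Fisher two-sided p = 0.158, not significant.
- Newcombe upper limit = d + √[(u₁ − p₁)² + (p₂ − l₂)²]. At the 97.5% level the Wilson upper limit for 20/70 is u₁ = 0.4178 and the Wilson lower limit for 12/70 is l₂ = 0.0935.
- Result: 0.1143 + √[(0.4178 − 0.2857)² + (0.1714 − 0.0935)²] = 0.1143 + 0.1534 = 0.268, or 26.8 points. The 95% upper limit is 24.9 points.

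Fisher finds no significant difference, while an excess well above 15 points remains compatible with the data.

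**4. When the stems are truly equal at 20%.** With 70 per group, Fisher is non-significant in 98.6% of trials at 0.025 and 96.9% at 0.05. The Newcombe rule declares non-inferiority in 49.6% (97.5% interval) or 60.5% (95% interval). The two analyses part company, with Fisher non-significant but the upper limit at or above 15 points, in 49.7% of trials at the 0.025 level and 38.0% at the 0.05 level.

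The normal approximation agrees on power. The standard error is √(0.32/70) = 0.0676 and 0.15/0.0676 = 2.219. Then Φ(2.219 − 2.241) = 0.49 and Φ(2.219 − 1.960) = 0.60.

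**The case against.** **The Abstract promises an effect-size interval.** A reader might infer that the plan as a whole cannot answer the trial's question. The article does not support that. The Abstract's 95% intervals are not restricted to secondary outcomes, and an analyst could set one beside the 15% limit. What stands is narrower: the named test does not use the limit, no sentence links the interval to it, and the interval's level differs from the declared alpha.

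**This is a condensed article.** The interval method, the adjusted model and the detailed decision rule are commonly left to a fuller document. For that reason the Analysis section's failure to repeat the Abstract's interval and regression is not counted as an error here. The objection does not cover the test itself, because the article names one and it belongs to a different hypothesis.

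**The harm assumes a misreading.** A reader might infer that the trial will declare non-inferiority from a non-significant p value. The article never says so. The 67% and 56% are error rates of that reading, not of a stated rule.

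**Disagreement when the stems are equal.** The 49.7% and 38.0% mainly reflect low power of the interval rule at 70 per group. They are a sample-size consequence and are not evidence against Fisher's test.

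**Conclusion.** The point holds in this form: the article names a test of equal rates for an endpoint that it frames and sizes for non-inferiority, and the Abstract's interval is tied neither to the 15% limit nor to the alpha of 0.025. This is an analysis stated wrongly, not a detail left out, and it concerns a primary endpoint, so it should be corrected.

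The size is conditional. If non-significance were taken as non-inferiority at 35% against 20%, the error would be 67% (alpha 0.025) or 56% (0.05), against about 1.4% or 2.7% for a Newcombe rule. This rests on 70 evaluable patients per group, a cemented rate of 20% and an absolute limit. The mismatch between test and hypothesis does not depend on those figures, nor on whether 60 per group can be reproduced.

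**What to change.** In the Analysis section, replace the Fisher sentence with a primary analysis along these lines:

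- **Measure:** the risk difference, uncemented minus cemented, in the proportion of patients with at least one hip-related complication by 2 years.
- **Interval:** a two-sided 97.5% score-type interval, matching the declared alpha. Newcombe or Miettinen-Nurminen would serve, and other valid score-type methods are acceptable. It should preferably account for the stratification by sex.
- **Rule:** conclude non-inferiority only if the upper limit is below 15 percentage points.
- **Fisher's test:** keep it as a secondary test of difference.

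Bring the Abstract's interval level into line with this, or explain why it differs.

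**Cost.** The change is to analysis wording and needs no new data or visits. It does require a disclosure: with 20% in both arms, the rule has about 50% power at 70 per group, or about 60% with a 95% interval, and not the stated 80%.
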